### Data collection, management

Data will be collected using questionnaires deployed on Open Data Kit (ODK, https://opendatakit.org/) software installed on tablet computers, which will automatically be stored on a managed Google engine server. Information will be transferred to a central database server by a trained technical data coordinator on a daily basis for quality assurance. All the study interviewers will be trained on the ODK survey system.

### Data analysis

The unit of analysis will be children between the ages of 5 to 15 years, who are most vulnerable for the development of NS/OAE. The incidence rate of NS/OAE at baseline will be calculated using incident cases in children 5 to 15 years of age during the preceding 24 months. This rate will be compared with the incidence rate of NS/OAE in the 24-month interval between the first and the second household surveys.

Data will also be collected on recent deaths that might be attributed to recent onset NS and other forms of epilepsy (household heads and community informants will be questioned). Deaths suspected to be because of NS/OAE will be considered as incident cases.

Descriptive statistics will be employed to present retention rates. Means and standard deviations will be presented for continuous outcome measures and frequencies and percentages will be presented for categorical variables. Chi-squared tests will be used to compare any group differences for categorical variables and *t*-tests will be used for continuous variables.

The incidence of NS/OAE pre- and post-intervention will be compared among those who received ivermectin twice a year over 2 years and those who missed at least one dose of ivermectin.

Conflict induced displacement of people during the study period is possible. In case of in or out migration only the data will be analysed of families who stayed for at least 5 years in the area.

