**Fig. 2 Fig2:**
[figure not shown]
Western Equatoria State Map showing the location of Mundri and Maridi

Mundri and Maridi have a high prevalence of NS and other forms of epilepsy [4, 12, 13]. The population of Mundri (East and West) and Maridi Counties are estimated at 82293 and 101 065 respectively [24]; farming is the main economic and livelihood activity. A small proportion of the population practise cattle herding and fishing. Water is mainly accessed from the Yei and Maridi Rivers, which are rapidly flowing and provide sufficient breeding sites for the *Simulium* vector (blackfly) that transmits *Onchocerca volvulus*. As a result of the recent civil conflicts in South Sudan, which also affected the study area, population movement in and out of the area has been high. However, most of the population did not leave the area but rather sought shelter in nearby villages that were considered safe [25]. This might also have been the case throughout the long period of the civil war that lasted for over 20 years before the peace agreement in 2005. The study will only include participants in villages that have lived in the area for at least 5 years.

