### Sample size

We expect a crude incidence of new onset cases of NS/OAE in the Mundri/Maridi areas to be about 1.67% per year in all children aged five to 15 years [31]. With > 90% coverage of eligible individuals and 100% geographical coverage in the study area, we expect to decrease the incidence of NS/OAE in the five to 15-year-old population by 50%. Based on the reference proportion of 0.0150 (1.5% per year), alpha 5%, statistical power 80%, 2-sided testing, a total of 3475 children aged five to 15 years old need to be included in the study.

An adaptive study design will be used to ensure an adequately powered study. The NS/OAE incidence data will be cleaned after around 3000 children have been enrolled. The required sample size will be re-calculated using the actual observed incidence rate to ensure the study is adequately powered.

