### Limitation

A challenge for the study will be the insecurity in the region and the migration of people as a consequence. Ideally a clustered randomised controlled trial would be preferred in which one population receives ivermectin treatment and the other not. However, given the expected benefits of CDTi, withholding treatment is ethically not acceptable. Indeed in onchocerciasis-endemic regions all eligible individuals should receive ivermectin at least annually [32]. Comparing annual with bi-annual ivermectin treatment would be a possibility but this would require a very large sample size because of the relatively low incidence of epilepsy. Moreover, to achieve the elimination goal for onchocerciasis and based on success stories from the Americas and other African countries, a bi-annual CDTi strategy is preferred, especially where the onchocerciasis situation is insufficiently controlled [33–35]. Given the dramatic decrease of incidence of NS/OAE as a consequence of bi-annual CDTi and larviciding of rivers in northern Uganda [36], we expect that with an optimal bi-annual CDTi programme with > 90 coverage of eligible individuals, we will be able to show a similar decrease of incidence of NS/OAE in South Sudan.

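### The pre/post NS/OAE comparison has no village term, and the residence rules do not hold the village mix constant, so displacement could mix a composition change into the CDTi ratio.

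*Protocol article*

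**What the plan says.** All of this is in the protocol article.

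- **Comparison (Data analysis).** The child is the unit of analysis. "The incidence rate of NS/OAE at baseline will be calculated using incident cases in children 5 to 15 years of age during the preceding 24" (in months). That rate is compared with the rate in the 24 months between the household surveys. Chi-squared is the only test named for categorical data. No stratification, weighting or pairing by village is mentioned.
- **Movement.** Data analysis states: "Conflict induced displacement of people during the study period is possible". The Limitation section adds: "A challenge for the study will be the insecurity in the region and the migration of people as a consequence". Study setting says of the recent conflict that "most of the population did not leave the area but rather sought shelter in nearby villages that were considered safe".
- **Safeguards.** Study setting selects villages whose population has not been displaced. The inclusion criteria take families who do not plan to leave within two years. If there is migration, Data analysis keeps only families with at least 5 years in the area.

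**The concern.** An overall rate is an average of village rates weighted by each village's share of children. If villages differ in incidence and their shares change between periods, the ratio moves even when no village's own rate has changed. This shifts the point estimate and is separate from any question about standard errors.

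The safeguards leave three gaps:

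1. The 5-year rule counts time in the area, not in the village. A family that moves to a nearby village stays eligible.
2. The rule does not cover a village that cannot be reached at the second survey.
3. It is unclear whether families who leave are also removed from the baseline rate.

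The study is an uncontrolled before-after comparison, so no concurrent group would absorb such a shift. The direction depends on which villages lose children and cannot be known in advance.

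**Working it through.** **The plan's own figure.** The sample size section gives "alpha 5%, statistical power 80%, 2-sided testing, a total of 3475 children aged five to 15 years old need to be included", with a reference proportion of 0.015 per year and a 50% reduction, so 0.0075. The usual two-proportion formula is

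n = [1.96√(2p̄(1−p̄)) + 0.8416√(p₁(1−p₁) + p₂(1−p₂))]² / (p₁−p₂)², with p̄ = 0.01125.

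This gives (0.2923 + 0.1254)² / 0.0075² ≈ 3104 per period, or 3365 with continuity correction. The figure 3475 is not reproduced. That is a separate matter; 3475 serves below only as an assumed number of children at baseline.

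**Assumptions (not in the documents).** High-risk villages hold a share w of children at baseline and have r times the risk of the others. They lose a fraction l of their children before follow-up, and the other villages lose none. Leavers stay in the baseline rate. CDTi has no effect. I take w = 0.25 to 0.50 and r = 2 to 3.

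**Formula.** Crude ratio = {[w(1−l)r + (1−w)] / [w(1−l) + (1−w)]} / [wr + (1−w)]

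Example, w = 0.5, r = 3, l = 0.5: (0.75 + 0.5)/(0.25 + 0.5) = 1.667; baseline 1.5 + 0.5 = 2.0; ratio 1.667/2.0 = 0.833.

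| w | r | l = 10% | l = 20% | l = 50% | l = 100% |
|---|---|---|---|---|---|
| 0.25 | 2 | 0.985 | 0.968 | 0.914 | 0.800 |
| 0.25 | 3 | 0.974 | 0.947 | 0.857 | 0.667 |
| 0.50 | 2 | 0.982 | 0.963 | 0.889 | 0.667 |
| 0.50 | 3 | 0.974 | 0.944 | 0.833 | 0.500 |

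If instead the low-risk villages lose half their children, the ratio is 1.11 to 1.20.

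**Chance of a significant false reduction.** Take a 24-month risk of 2 × 1.5% = 3.0%, 3475 children at baseline, and a follow-up sample that shrinks with the losses. Under a normal approximation the probability is Φ[(p₁ − p₂ − 1.96·SE₀)/SE₁], where SE₀ is pooled and SE₁ unpooled. For w = 0.5, r = 3, l = 0.5: p₂ = 0.025, n₂ = 2606, SE₀ = 0.00427, SE₁ = 0.00421, so Φ(−0.80) = 0.21.

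The four half-loss cases, in table order, give 0.09, 0.18, 0.12 and 0.21, against a nominal 0.025. At 10% to 20% loss the range is 0.03 to 0.06. Complete loss with w = 0.5 and r = 2 gives 0.56 (about 0.62 with an unpooled standard error throughout).

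**Same example, stratified by village.** An overall 3.0% with r = 3 and w = 0.5 means 1.5% and 4.5%.

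- Low-risk stratum: 26.06 cases in 1737.5 children in each period.
- High-risk stratum: 78.19 cases in 1737.5 before, 39.09 in 868.75 after.

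Mantel-Haenszel numerator: 26.06×1737.5/3475 + 39.09×1737.5/2606.25 = 13.03 + 26.06. Denominator: 26.06×1737.5/3475 + 78.19×868.75/2606.25 = 13.03 + 26.06. The ratio is 1.00, where the crude ratio is 0.833.

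**The case against.** **The safeguards may be enough.** The migration rule names out-migration. Read naturally, it could remove leavers from both rates, so that both rest on much the same stable families and the mix hardly changes. This stands as a limit on size: the table assumes that leavers stay in the baseline rate. It does not close the point, because the text does not say the rule applies to the baseline rate and is silent on an unreachable village.

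**The background prevalences do not show village differences.** A reader might take 4.6%, 8.4% and one in six as a spread of village risk. The documents do not support that. The first is NS alone in 2001, the second is all epilepsy, and the third is all epilepsy in children in 2013. They are prevalences, and the article calls the second consistent with the third. Better but unquantified signs are that the OAE definition uses high epilepsy prevalence in the village as a criterion, and that very high nodule prevalence is reported for only some villages.

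**Losses of half or more are severe.** No section predicts them. At 10% to 20% the distortion is small beside the planned 50% reduction. This stands.

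**Movers may carry their risk.** If past exposure determines risk, a move between study villages leaves the pooled rate unchanged, and assigning movers to their current village would put them in the wrong stratum. This stands and shapes the fix.

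**Model detail belongs in an SAP.** The article does not exclude an adjusted analysis, and its silence on a model is not the point here. It does state the comparison and a migration rule, and that rule does not do the work needed.

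**Conclusion.** The point holds in limited form. As stated, the comparison does not hold village composition constant, and the safeguards reduce the problem without removing it. With no true effect, the crude ratio would be about 0.94 to 0.98 under modest differential loss, 0.83 to 0.91 if high-risk villages lose half their children, and 0.50 to 0.80 if they drop out. These figures rest on assumed village shares, risk ratios and losses, and on leavers staying in the baseline rate.

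A reader might infer that the ratio would track village mix and not CDTi, or that mix could by itself produce the planned halving. Neither is supported. With a common CDTi effect, the crude ratio is the true ratio times the mix factor: a true 0.50 with a factor of 0.833 would appear as 0.42. Mix alone reaches 0.50 in this range only at r = 3, w = 0.5 and complete loss.

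**What to change.** In Data analysis:

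- Make the main estimate a village-stratified (Mantel-Haenszel) rate ratio, or a Poisson model with village as a fixed factor, using in both periods only villages surveyed both times.
- Apply one residence rule identically to both rates, and say whether families who leave are removed from the baseline rate. The three years in the inclusion criteria and the five years in Study setting and Data analysis need to be reconciled for this.
- Assign children who move between study villages to their baseline village, with current village as a sensitivity analysis.
- Report the crude ratio beside the stratified one.

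This should be fixed before follow-up data are seen.

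Cost: villages not re-surveyed leave the main ratio, so precision falls in proportion to their share of children (25% to 50% in the complete-loss cases above), and the result applies only to villages surveyed twice. Village must be recorded for each household at both surveys, and baseline village for movers. The door-to-door design implies the former, but the article does not state either.

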## Abstract

**Background:**

Nodding syndrome (NS) is a devastating epileptic illness of unknown aetiology mainly affecting children 5–15 years of age. Head nodding distinguishes NS from other forms of epilepsy. Other manifestations of the illness include mental and physical growth retardation. Many children die as a result of falling in fires or drowning. Recently, it was shown that NS is only one of the phenotypic presentations of onchocerciasis associated epilepsy (OAE). Despite the strong epidemiological association between epilepsy and onchocerciasis, the causal mechanism is unknown. After implementation of bi-annual community directed treatment with ivermectin (CDTi) and larviciding of rivers in northern Uganda, new cases of NS have ceased, while new cases continue to emerge in South Sudanese onchocerciasis-endemic areas with an interrupted CDTi programme. This study is designed to evaluate the potential effects of bi-annual CDTi on reducing the incidence of NS/OAE in onchocerciasis-endemic areas in South Sudan.

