##### Definitions

A *case of epilepsy* will be defined based on the International League Against Epilepsy (ILAE) as an individual with at least two unprovoked seizures with a minimum of 24 h separating the two episodes [27].

*Active epilepsy* will be defined as a person who is taking anti-epileptic treatment or who is not on anti-epileptic treatment but had at least one episode of seizures during the last 5 years.

A *new case of epilepsy* will be defined as a person who developed the first seizures within the last 24 months preceding the baseline survey (pre-CDTi incidence), or a person who developed the first seizures after the first round of CDTi and the second study visit to the household (post-CDTi incidence).

A *suspected NS case* will be defined as a person who presented with episodes of reduced consciousness with the head dropping forward repeatedly.

*OAE* will be defined as a person meeting the following six criteria: 1) Three years of living in an onchocerciasis-endemic region; 2) High prevalence of epilepsy in the village and families with more than one child with epilepsy; 3) History of at least two unprovoked epileptic seizures at least 24 h apart; 4) No obvious cause for the epilepsy; 5) Onset of epilepsy between the ages of three and 18 years; 6) Normal psychomotor development before the onset of epilepsy.

Epilepsy caused by perinatal trauma, head trauma, meningitis/encephalitis, and cerebral malaria can be suspected through medical history taking. Epilepsy caused by cysticercosis is difficult to differentiate from OAE but in the Maridi and Mundri areas there are no pigs, therefore neurocysticercosis does not exist in these areas. It is expected that the prevalence of epilepsy not caused by onchocerciasis will be < 1.4% (the median prevalence of epilepsy in Sub-Saharan Africa) [28].

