#### Follow up of epilepsy cases

The person with epilepsy will be asked to come to the health centre to initiate anti-epileptic treatment. At the health centre, the person or caretaker will be counselled about epilepsy, and anti-epileptic treatment according to WHO epilepsy guidelines and the NS management guidelines proposed by R Idro [29] will be started.

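### Deaths suspected to be due to NS/OAE count as incident cases without a stated onset window, so deaths in longer-standing epilepsy can enter the before-after incidence comparison

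*Protocol article*

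**What the plan says.** **Living cases.** Under Definitions in the protocol article, a new case before the intervention is "a person who developed the first seizures within the last 24 months preceding the baseline survey (pre-CDTi incidence"). The post-intervention definition is also anchored on first seizure, between the first treatment round and the second household visit. Under Confirmation of cases, a clinical officer or doctor confirms or rejects each suspected case. OAE has six criteria, including age at onset and absence of an obvious cause.

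**The comparison.** Under Data analysis, the baseline rate "will be calculated using incident cases in children 5 to 15 years of age during the preceding 24 months". Then: "This rate will be compared with the incidence rate of NS/OAE in the 24-month interval between the first and the second household surveys".

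**Deaths.** The next paragraph of the same section says: "Data will also be collected on recent deaths that might be attributed to recent onset NS and other forms of epilepsy", with heads of household and community informants as the source. The counting rule follows: "Deaths suspected to be because of NS/OAE will be considered as incident cases". It has no onset date, no age at onset and no reference to the case definitions.

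**Background facts.** The abstract says of the illness: "Many children die as a result of falling in fires or drowning". Under Follow up of epilepsy cases: "The person with epilepsy will be asked to come to the health centre to initiate anti-epileptic treatment".

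**The concern.** The numerator of the main comparison has two entry rules. A living child enters by date of first seizure. A dead child enters by suspected cause of death, with onset described at most as recent. A child whose seizures began three or four years earlier and who drowned inside the window could be counted by one field team and left out by another, and each could claim to follow the text.

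To the extent that such deaths are counted, the outcome mixes new onset with mortality among existing cases. The study has no concurrent control, so a difference in the leak between periods cannot be separated from the effect of ivermectin. Two features could make it differ:

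- The baseline survey lists existing cases. A later death in a listed person can be recognised as an old case. A death before baseline has no earlier list to be checked against.
- Identified cases are asked to start anti-epileptic treatment after the baseline survey, so mortality among existing cases may change when ivermectin distribution begins.

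If the counted old-case deaths stay stable, they dilute a real effect. If fewer are counted after baseline, they mimic one.

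**Working it through.** The plan gives no figure for deaths, so there is nothing of its own to reproduce here. The size below is an illustration.

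**Inputs from the protocol article**
- Children aged 5 to 15: 3475 (Sample size), taken here as the number observed in each period. The ratios do not depend on it.
- Reference incidence 1.5% per year (Sample size), so 3% over 24 months.
- Expected effect: a 50% reduction (Sample size).
- Epilepsy prevalence 8.4% (Burden of NS/OAE in South Sudan), applied to the children as an approximation.

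**Assumptions**
- Mortality m among existing cases is 1% to 5% per year.
- All these deaths are counted as incident. This ignores the recent-onset wording completely and is an upper bound. The 8.4% also includes some cases with onset inside the window.

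**Step 1: counts**
- True baseline onsets: T = 3475 × 0.03 = 104.25.
- Existing cases: 3475 × 0.084 = 291.9.
- Deaths over 24 months: D = 291.9 × 2m, which is 5.8 at 1% and 29.2 at 5%.

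**Step 2: no ivermectin effect, old-case deaths halve after baseline**
- Ratio = (T + D/2)/(T + D).
- Low: (104.25 + 2.92)/(104.25 + 5.84) = 107.17/110.09 = 0.97.
- High: (104.25 + 14.60)/(104.25 + 29.19) = 118.85/133.44 = 0.89.

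**Step 3: no ivermectin effect, old-case deaths counted before baseline but all recognised as old afterwards**
- Ratio = T/(T + D).
- 104.25/110.09 = 0.95 to 104.25/133.44 = 0.78.

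**Step 4: true ratio 0.50, old-case deaths unchanged**
- Ratio = (T/2 + D)/(T + D).
- (52.13 + 5.84)/110.09 = 0.53 to (52.13 + 29.19)/133.44 = 0.61.

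**Step 5: chance of a falsely significant benefit in the setting of Step 2**
- Normal approximation: Φ[(p₁ − p₂)/se − 1.96], with se = √{[p₁(1 − p₁) + p₂(1 − p₂)]/3475}. The nominal value is 2.5%.
- About 5, 10 or 21 old-case deaths, halved afterwards, give ratios of 0.976, 0.955 and 0.917, and chances of 3.8%, 5.4% and 10.1%.

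**Step 6: sensitivity to prevalence**
- Using the one-in-six figure, existing cases are 3475/6 = 579.2, and D at 5% is 57.9.
- Step 2 becomes (104.25 + 28.96)/162.17 = 0.82. Step 4 becomes (52.13 + 57.92)/162.17 = 0.68.
- That figure comes from a small household survey in Mvolo, not from the study counties, so it is an extreme.

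**Step 7: with the onset condition applied**
- Old-case deaths leave the numerator, so the null ratio is 1.00 whatever happens to mortality among existing cases. The sample size does not change.

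**The case against.** **The preceding sentence limits the rule.** It restricts data collection to recent deaths linked to recent-onset disease, and the counting rule can be read as acting on those deaths only. This objection largely stands. A reader who takes the counting sentence alone might infer that every suspected death is incident whatever its onset date. The documents do not support that. What remains is that "recent" has no limit, is not tied to either window, and is not repeated in the rule that does the counting.

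**Treatment need not lower mortality.** A reader might infer that counted deaths will fall once anti-epileptic treatment starts, producing a false ivermectin effect. The documents give no mortality rate, no treatment uptake and no effect of treatment on deaths, and they say only that people are asked to attend. A fall is possible, not established, and stable deaths bias towards no effect.

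**Counting deaths has a purpose.** A child who developed epilepsy and died within the window would be missed by a survey of the living, and the dead cannot be examined. This stands. The lack of clinical confirmation is not the flaw, and deaths should not simply be dropped.

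**An article condenses the full protocol.** The wording of the death interview and any sensitivity analysis may well be set out elsewhere, and their absence is no finding. But the article does state the counting rule, and as stated it does not match its own definition of a new case.

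**Conclusion.** The point holds in limited form. The rule for deaths lacks the onset condition that defines a living new case, and the undefined recent-onset wording narrows the gap without closing it. Deaths in longer-standing epilepsy can enter the main comparison, and the leak may differ between the two periods.

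The likely bias is modest, and its direction cannot be settled from the documents. At 8.4% prevalence and an assumed mortality of 1% to 5% per year, the upper-bound effect is a null ratio of about 0.97 to 0.89 if the deaths halve, or a true 0.50 read as about 0.53 to 0.61 if they do not change. Real values should be closer to the truth than these, because some old-case deaths would be screened out even under the present wording.

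The leak cannot alone explain a 50% fall. With the deaths halved, (T + D/2)/(T + D) always stays above 0.50. Even if such deaths were counted only before baseline, D would have to equal the roughly 104 true onsets. The point deserves correction because it touches the main outcome and is cheap to fix, but it does not by itself undermine the study.

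**What to change.** Replace the counting sentence with a rule that matches the definition of living cases:

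- Count a death as incident only if the informant places the first seizure inside the same 24-month window and within the analysed age band, and the reported history is consistent with the OAE criteria.
- At the second survey, exclude deaths among people recorded with epilepsy at baseline.
- Report the rate ratio with and without deaths. The analysis without deaths is a check and not a replacement, because it loses true new cases who died.
- Use deaths with unknown onset in a sensitivity analysis only.

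The cost is one or two onset questions in the death interview, a sentence or two of wording, and a few deaths moved to the sensitivity analysis. The sample size is unaffected. The questions should be in place for the baseline interview, since onset dates not asked then would be hard to recover two years later.

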### Burden of NS/OAE in South Sudan

Since the first cases of NS were reported from the Western Equatoria region of South Sudan in the 1990s, the region has continued to have a high rate of new NS cases and other forms of epilepsy. In 2001, the World Health Organization (WHO) estimated the prevalence of NS to be at 4.6% among a small population in Western Equatoria, which is considered to have the highest burden of the disease [4]. During a small household survey conducted in 2013 in the same area (Mvolo), one in six children had epilepsy (NS and other forms of epilepsy), one in two households had at least one child with epilepsy, and one in three households had at least two children with epilepsy [12]. The South Sudan Relief and Rehabilitation Commission reported an epilepsy prevalence of 8.4% (including NS and other forms of epilepsy), consistent with the 2013 household survey [13].

As part of an initiation visit for a study on NS in Lui, Mundri East (June 2016), we conducted house-to-house interviews in communities living around Lui hospital. We randomly selected households and detected cases of NS and other forms of epilepsy in about half the households, with some households having more than one person with epilepsy, as was observed in Mvolo.

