## Study design

### Prevalence and incidence of NS and other forms of epilepsy

#### Population-based survey

In order to determine the prevalence and incidence of NS and other forms of epilepsy, a population-based household survey will be conducted prior to bi-annual CDTi.

The survey will start by short questionnaire-based interviews with village leaders and village health workers to capture village demographic information.

All individuals in the selected villages will be included in a door-to-door survey. A two-step epilepsy survey will be used to identify cases of NS and other forms of epilepsy. For screening, a pre-tested validated questionnaire for epilepsy consisting of five specific questions will be used [26].

The surveys will be planned when there are no major farming activities ongoing to obtain information on all people living in the village. If at the time of the home visit nobody is at home this household will be revisited later, at least once.

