### Study inclusion criteria

All members of families who have lived for at least three years in the villages and are not planning to leave the village in the next two years.

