### Study procedures

Pre- and post-intervention household surveys will be performed using exactly the same methodology. The pre-intervention survey will be done within two months before the start of the bi-annual CDTi. A post-intervention survey will be done 2 years later.

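### The only test named for binary comparisons treats children as independent, so the 5% error rate of the before-after comparison is not assured, and the article does not settle in which direction it errs.

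*Protocol article*

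**What the plan says.** All of this is in the protocol article.

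- Data analysis, unit: "The unit of analysis will be children between the ages of 5 to 15 years".
- Data analysis, main comparison: incidence in the 24 months before baseline is calculated, and then "This rate will be compared with the incidence rate of NS/OAE in the 24-month interval between the first and the second household surveys". That sentence names no test.
- Data analysis, second comparison: incidence is compared between "those who received ivermectin twice a year over 2 years and those who missed at least one dose of ivermectin".
- Data analysis, tests: "Chi-squared tests will be used to compare any group differences for categorical variables". The only other test named is the t-test, for continuous variables.
- Population-based survey: "All individuals in the selected villages will be included in a door-to-door survey".
- Study procedures: "Pre- and post-intervention household surveys will be performed using exactly the same methodology", two years apart.
- Study inclusion criteria: families already resident for three years and "not planning to leave the village in the next two years".
- Burden of NS/OAE in South Sudan, on a small 2013 survey in Mvolo in which one child in six had epilepsy: "one in two households had at least one child with epilepsy, and one in three households had at least two children with epilepsy".
- Definitions: the second OAE criterion refers to high village prevalence and to families with more than one affected child.

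The article does not mention village or household clustering in the analysis, pairing of the two surveys, a design effect or a confidence interval. Under Limitation it calls a clustered randomised trial the ideal design, but no clustering reaches the analysis or the sample size.

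**The concern.** A two-proportion chi-squared test takes each child in each window as an independent observation. Three features of this design contradict that.

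1. Sampling and ivermectin distribution are by village, and children in a village share exposure to the same breeding sites.
2. Cases aggregate in families on the article's own evidence. The second OAE criterion also makes case classification depend on village and family.
3. The two windows draw on the same villages and households, and on many of the same children.

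There is no control group, so the before-after contrast carries the whole conclusion, which the Discussion intends for policy makers and funders. If its standard error is wrong, so is the p-value on which a claimed reduction would rest. The dosing comparison is exposed as well, because uptake is likely to differ between villages.

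Two lesser points follow from the same choice. A chi-squared test on children does not use time at risk, although the outcome is called a rate. It also cannot adjust for age if the mix of ages differs between windows.

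**Working it through.** **The plan's own figure.** Sample size inputs: 1.5% per year, halved to 0.75%, two-sided 5%, power 80%. The standard formula for two independent proportions gives 3104 per survey, or 3365 with continuity correction. The article states 3475 in total, and its stated inputs do not reproduce that figure. What matters here is that the stated inputs include no design effect, and that the planned re-calculation after about 3000 children updates only the incidence.

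**Does familial clustering exist?** Inputs from the Burden section: prevalence 1/6, half of households with at least one affected child, one third with at least two.
- Under independence, the household size that gives one half is k = ln(0.5)/ln(5/6) = 3.80 children.
- P(at least two) = 0.5 − (k/6) × (5/6)^(k−1) = 0.12, against 0.33 reported.
- A beta-binomial model with prevalence 1/6 and an assumed 5, 6 or 7 children per household, fitted by least squares to 0.50 and 0.33, gives an intracluster correlation of 0.16, 0.20 or 0.25. The design effect 1 + (k−1) × ICC is then about 1.7, 2.0 or 2.5.
- The fit is imperfect: it yields 22%, 27% or 30% of households with at least two cases, short of 33%. Unequal household sizes could explain part of the excess.

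So clustering is present, but these are prevalence figures and do not carry over to incidence.

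**Why the direction is open.** Var(post − pre) = Var(post) + Var(pre) − 2 Cov(pre, post). Clustering raises the first two terms. Village or household risk that persists across windows raises the covariance and takes the excess away again. Chi-squared ignores both.

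**Size if the covariance does not help.** Actual error = 2 × (1 − Φ(1.96/√DE)), with DE = 1 + (m−1) × ICC. The article gives no ICC and no village size, so all values of m and ICC are assumed.

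| Assumed setting | DE | Actual error |
|---|---|---|
| Households of 3, ICC 0.01 | 1.02 | 5.2% |
| Households of 3, ICC 0.10 | 1.20 | 7.4% |
| Villages of 50, ICC 0.01 | 1.49 | 10.8% |
| Villages of 100, ICC 0.01 | 1.99 | 16.5% |

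The rounded design effects 1.2, 1.5 and 2.0 give 7%, 11% and 17%. For the before-after contrast these are upper bounds at the given m and ICC, because the same villages appear twice.

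**Simulation under no effect**, about 3475 children per survey, nominal 5%, risk of 1.5% or 3%, all variation assumed (CV = coefficient of variation of risk):

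| Scenario | Actual error |
|---|---|
| Villages differ (CV 0.5 to 1), same risk in both windows | 4.5% to 5.0% |
| Households of 3 (CV 2 to 3), same risk in both windows | 2.4% to 4.0% |
| Households of 3 (CV 2 to 3), risk independent by window | 6.2% to 11.7% |
| 35 villages of 100, village risk shifts between windows, CV 0.25 / 0.5 / 1.0, at 1.5% risk | 6% / 10% / 24% |
| 17 villages of 204, same shifts, at 1.5% risk | 7% / 16% / 37% |
| Fully dosed versus missed a dose, uptake varying by village (CV 0.5 to 1) | 5.8% to 17.5% |

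**The case against.** The chi-squared sentence sits in a general paragraph that begins with retention rates and descriptive summaries; the sentence on the main comparison names no test. The full protocol or an analysis plan may specify a model. The sentence on the unit could also be read as setting an age group. This stands in part: the link is an inference. But the sentence covers any group difference in a categorical variable, it is the only applicable test named, and following the article as written leads to it.

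A reader might infer that the test must overstate significance. The documents do not support that. Household aggregation of the kind reported from Mvolo, if it persists, makes the before-after test conservative, and a conservative test still keeps its error below 5%. Inflation needs variation between windows, whose size the article does not give. It is plausible, since the article expects conflict and displacement, but it is not established.

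A reader might also take 1.7 to 2.5 as the design effect for this study. It is not: it describes prevalence in a small survey outside the study counties, with assumed household sizes and an imperfect fit. The article's own visit to Lui, in Mundri East, reports a similar household pattern but gives no comparable figures.

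Nor can a planned confidence interval be called invalid, because the article plans none. The point applies only to an interval built on the same independence assumption.

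The time-at-risk and age points are secondary. Both windows are 24 months, and the text does not settle whether a closed cohort or two repeat surveys of ages 5 to 15 is meant, so an ageing cohort cannot be assumed.

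**Conclusion.** The point holds in a limited form. The article fixes the child as unit and names only a test that assumes independence, in a design with village sampling, family aggregation and repeated villages. The nominal 5% level is therefore not assured.

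The size is open. Under assumed values it runs from about 2% to 5% when village or household risk is stable, to 7%, 11% or 17% at design effects of 1.2, 1.5 or 2.0, and higher in simulation if village risk shifts strongly between windows with few villages. The dosing comparison does not gain from pairing across windows in the same way and came out anti-conservative in every simulated setting where village risk varied. All these figures rest on assumed correlations, household sizes and village numbers. What the article itself establishes is that clustering exists, not how large it is for incidence.

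**What to change.** State that the primary before-after comparison will account for village clustering and for the pairing of windows within villages. One suitable form:

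- a Poisson or GEE model of new NS/OAE cases;
- log of children or person-years at risk as offset;
- period as a within-village effect and age band as covariate;
- village-clustered standard errors with a small-sample correction.

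If villages are few, a paired village-level analysis is a sound alternative. Report the post/pre rate ratio with a 95% confidence interval. Apply the same clustering adjustment to the dosing comparison, and keep chi-squared tests for descriptive tables.

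The cost is a change of analysis wording and minor analysis work with routine software, provided that records carry a village identifier. The interval may be wider or narrower than under independence, depending on which source of correlation dominates.
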